#### Study Design

This is an open waitlist study whereby eligible participants will be assigned to a treating clinician and will complete 4 weeks of the CBT-SC-Peri treatment protocol, followed by a post-treatment assessment. If a treating clinician is not immediately available, participants will be placed on that clinician's waitlist for 4 weeks. They will then be re-assessed after the 4-week waitlist period and then undergo the four-session treatment, followed by a post-treatment assessment. For a flowchart of trial procedures, see Figure 1.

**Figure 1 F1:**
[figure not shown]
Flowchart of trial procedures.

### Procedure

#### Recruitment and Informed Consent

Participants will be recruited through the Women's Health Concerns Clinic (WHCC), St. Joseph's Healthcare (SJHH), a well-established clinical and research center dedicated to women's health issues, particularly those associated with reproductive life cycle events (e.g., perinatal, menopausal transition). The WHCC receives an average of 60–80 referrals per month, with 20 of those specifically related to the population addressed here. Additionally, referrals from the Fontbonne Menopause Clinic within SJHH will be included and recruitment from Hamilton and surrounding areas will take place via advertisement postings and local newspapers. This study will be conducted within the WHCC and has received approval by the Hamilton Integrated Research Ethics Board (HIREB #11152), in accordance with the Declaration of Helsinki.

The consent statement includes comprehensive details of the project such as information regarding the CBT-SC-Peri treatment, assessments, research procedure, potential risks, renumeration, confidentiality, and freedom to withdraw participation. After reading consent and allowed time to ask questions, participants provide their informed consent. Women who do not fulfill initial eligibility are directed to a list of further support services.

#### In Person vs. Virtual Study Visits

As this study will recruit participants from the Greater Hamilton and Toronto Area, and to ensure accessibility for participant's who may be unable to attend in-person visits (i.e., due to long distances, unable to travel), we will provide the option for virtual study visits. The WHCC has the capacity to provide appointments with participants through SJHH's virtual platform, Dovetale, which uses the Zoom Video Communications interface. Zoom provides videotelephony and online chat services through a cloud-based peer-to-peer software platform, used for teleconferencing, telecommuting, distance education, and social relations. Zoom claims to be compliant with the Personal Information Protection and Electronic Documents Act and the Personal Health Information Protection Act. If participants are taking part in a virtual visit for their first study visit, participants will be emailed a copy of the participant information and consent form prior to the first study visit. At the beginning of the first study visit, the interviewer will review the consent form with the participant, via the share screen function on Zoom, providing the opportunity for a question-and-answer period. Following review of the form, participants will be asked to sign and return the consent form, via email, while on Zoom. Once participants have signed and returned the consent form, interviewers will also sign the consent form, and return a copy to the participant via email, before commencing with the first study visit. A section describing virtual visits and the rules for participation are included in the Informed Consent Forms.

#### Telephone Screening and Study Visits

Women who are interested in participating will receive an initial telephone screen to ensure eligibility. Following informed consent, participants deemed eligible will be enrolled into the study and complete their baseline assessment consisting of a structured clinical interview (Mini International Neuropsychiatric Interview for DSM-5 and the Sexual Disorders Module of the Diagnostic and Research Tool for DSM-5) and self-report measures. Upon confirming eligibility at the baseline assessment, participants will be assigned to a treating clinician to undergo four weekly sessions (up to 90 min) of individual CBT-SC-Peri. If a treating clinician is not immediately available, participants will be placed on a waitlist for 4 weeks before starting treatment. Participants who are on the waitlist for treatment will be asked to complete the self-report measures following the waitlist period/before starting treatment. To reduce attrition, participants will be compensated with a $20 gift card following each assessment visit at baseline, post-waitlist (for those in the waitlist group), and post-treatment, in addition to travel reimbursement via the form of a parking pass or bus tickets (if an in-person visit is conducted).

Because of the short duration of the treatment and the sensitive nature of the topic (sexual concerns), there may be an unintended effect of the study namely, no improvement or worsening of symptoms. Should this occur, the research participant will be offered further care by our treatment team within the WHCC, a clinic that is equipped with a multidisciplinary team including psychiatrists, obstetricians-gynecologists, and psychologists.

### Study Measures

The assessment battery includes various measures of sexual concerns, vasomotor symptoms, mood, anxiety, relationship, health, body image, cognitive flexibility, and treatment satisfaction. The primary outcome of this trial, sexual satisfaction, is assessed with the Female Sexual Desire Questionnaire. Please see Table 1 for a list of measures and their associated timing.

**Table 1 T1:** Timing of measurements.

**Procedures and Measures**	**CBT-SC-PERI**		**Waitlist** **+** **CBT-SC-PERI**		
	**Baseline**	**Post-treatment**	**Baseline**	**Post-waitlist**	**Post-treatment**

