Given the high rates and associated impairment of sexual concerns during perimenopause, we developed a CBT protocol specifically designed to target sexual concerns during perimenopause as a means of early intervention. Although decline in sexual function and satisfaction naturally decreases with age (13), this decline may also significantly reduce quality of life. As a result, we aim to address sexual concerns earlier in the menopausal transition with the goal of both improving sexual satisfaction, as well as reducing the impact on one's quality of life to improve future outcomes. The primary objective of this study is to evaluate the efficacy of this weekly, four-session, individual CBT for sexual concerns in perimenopause (CBT-SC-Peri) protocol. It is hypothesized that the CBT-SC-Peri protocol will significantly improve sexual satisfaction (primary outcome), desire, arousal, relationship satisfaction, body image, vasomotor symptoms, depression, and anxiety (secondary outcomes). To our knowledge, this will be the first study to investigate the efficacy of a CBT protocol (CBT-SC-Peri) specifically aimed at improving sexual concerns and associated distress experienced during perimenopause. As consumer demand increases for non-pharmacological treatments for perimenopausal symptoms, this form of treatment may not only be preferred by some, but necessary for others as hormonal treatments commonly have associated adverse effects and/or are contraindicated for some women.

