**Primary Outcomes**					
Female Sexual Function Index	X	X	X	X	X

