**Secondary Outcomes**					
Female Sexual Distress Scale-Revised	X	X	X	X	X
Female Sexual Desire Questionnaire	X	X	X	X	X
Hamilton Anxiety Rating Scale	X	X	X	X	X
Hot Flash Related Daily Interference Scale	X	X	X	X	X
Beck Depression Inventory-II	X	X	X	X	X
Couples Satisfaction Index	X	X	X	X	X
36-Item Short-Form Health Survey	X	X	X	X	X
Dresden Body Image Questionnaire	X	X	X	X	X
Cognitive Flexibility Inventory	X	X	X	X	X

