### Primary Outcome

#### The Female Sexual Function Index

The Female Sexual Function Index (FSFI) (23) is a six-domain measure of female sexual functioning including sexual desire, subjective arousal, lubrication, orgasm, satisfaction, and pain. The FSFI has demonstrated excellent internal consistency (α = 0.82–0.96) and test-retest reliability when used in menopausal women (22–24). A clinical cut-off score of 26 or lower has been suggested to identify significant sexual dysfunction (22). The FSFI is considered as a gold-standard in assessing sexual functioning in women (25).

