#### Female Sexual Desire Questionnaire

The Female Sexual Desire Questionnaire (FSDQ) (27) is a 50-item self-report questionnaire assessing one's experience of and sexual desire for women across six domains: dyadic desire, solitary desire, resistance, positive relationship, sexual self-image, and concern. The FSDQ has demonstrated excellent internal consistency across domains (α = 0.80–0.92) and specifically measures both dyadic and solitary desire, which other questionnaires do not (27).

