### Statistical Analysis Plan

Treatment response will be determined using multiple measures, as identified in the assessment battery, and distinguished between primary and secondary efficacy analyses. A series of repeated measures analysis of covariance (ANCOVA) will be used to examine condition differences. A two (treatment vs. wait-list) by two (time: pre-treatment, post-treatment) repeated measures ANCOVA will be used to examine differences in both primary and secondary outcomes, specifically sexual satisfaction and desire, body image, partner satisfaction, vasomotor symptoms, as well as depression and anxiety symptoms. Covariates for all analyses will include age, current marital status, medication use at baseline, treatment delivery method, and baseline depression and anxiety severity. If continuous variables do not meet the assumptions of normality, as assessed by the Shapiro-Wilk test, we will use non-parametric methods, with alpha levels set at 0.05.

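### Study Measures assigns the primary outcome, sexual satisfaction, to the FSDQ, while Table 1 and the outcome sections make the FSFI primary; renaming the instrument alone would still leave construct and score unmatched

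*Protocol article*

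**What the plan says.** The article identifies the primary outcome in several places, and they do not agree.

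- **Study Measures, opening paragraph:** "The primary outcome of this trial, sexual satisfaction, is assessed with the Female Sexual Desire Questionnaire". The paragraph then refers the reader to Table 1.
- **Table 1:** the only row under the primary heading is "Female Sexual Function Index". The row "Female Sexual Desire Questionnaire" stands under the secondary heading.
- **Instrument sections:** the FSFI is the only instrument under Primary Outcome. It "is a six-domain measure of female sexual functioning including sexual desire, subjective arousal, lubrication, orgasm, satisfaction, and pain". The FSDQ is under Secondary Outcomes and is described as working "across six domains: dyadic desire, solitary desire, resistance, positive relationship, sexual self-image, and concern".
- **Introduction, last paragraph:** the hypothesis is that the treatment "will significantly improve sexual satisfaction (primary outcome), desire, arousal, relationship satisfaction, body image, vasomotor symptoms, depression, and anxiety (secondary outcomes". The Abstract gives the same split: satisfaction is primary, and desire is among the secondary outcomes.
- **Statistical Analysis Plan:** the repeated measures ANCOVA "will be used to examine differences in both primary and secondary outcomes, specifically sexual satisfaction and desire, body image, partner satisfaction", followed by further constructs. It names no instrument or score.

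**The concern.** A primary outcome needs one construct, one instrument and one score. Here the construct is stable (sexual satisfaction), the instrument is contradicted, and the score is not given.

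An analyst who followed the Study Measures sentence literally would test the primary hypothesis on a desire questionnaire that the same article ranks as secondary. By its listed domains, that questionnaire covers a construct which the hypothesis also ranks as secondary. An analyst who followed Table 1 would use the FSFI. Each could cite the protocol afterwards as support, so the protocol would not protect against choosing the instrument after seeing the results.

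The two instruments are not interchangeable. Participants are selected on the FSFI (26 or lower, Inclusion/Exclusion Criteria), so change in an FSFI score within each group is exposed to regression to the mean from that selection. The FSDQ plays no part in selection.

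**Working it through.** **Step 1. Set the statements side by side.**

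| Place | FSFI | FSDQ |
|---|---|---|
| Study Measures, text | not mentioned | primary |
| Table 1 | primary (only row) | secondary |
| Instrument sections | primary (only instrument) | secondary |
| Statistical Analysis Plan | not named | not named |

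Four placements (two for each instrument) point to the FSFI as primary. One sentence dissents.

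**Step 2. Match construct to instrument.** The FSDQ domains as listed are dyadic desire, solitary desire, resistance, positive relationship, sexual self-image and concern; none is named satisfaction. The FSFI domains as listed include satisfaction. The construct therefore also favours the FSFI.

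**Step 3. Match construct to score.** Satisfaction is one of six FSFI domains. The article introduces the FSFI as a measure of sexual functioning, and the only score it uses is the cut-off of 26, with no domain named. Two readings remain:

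- *FSFI satisfaction domain:* matches the stated construct and the listed instrument.
- *FSFI total:* matches the listed instrument, but its construct is sexual function, not satisfaction. It would also take in desire and arousal, which the hypothesis lists separately as secondary.

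Replacing one instrument name with the other in Study Measures would resolve Step 1 and leave Step 3 open.

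**Step 4. What a later choice between the two instruments would cost.** The article gives no figure to reproduce on this point. Inputs: a level of 0.05 (Sample Size; taken as two-sided, which the article does not state), two candidate instruments, and an assumed correlation ρ between the two test statistics, which the article does not give.

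If the two tests were independent: 1 − (1 − 0.05)² = 1 − 0.9025 = 0.0975.

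If they are correlated, with (Z₁, Z₂) standard bivariate normal with correlation ρ, the rate is 1 − P(|Z₁| < 1.96 and |Z₂| < 1.96):

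| Assumed ρ | Chance that at least one test is falsely positive |
|---|---|
| 0 | 9.75% |
| 0.3 | 9.5% |
| 0.5 | 9.1% |
| 0.7 | 8.3% |
| 0.9 | 7.0% |

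All of these exceed the nominal 5%.

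**The case against.** The strongest reply is that this is a one-word slip, Desire written for Function. Table 1 and the section structure agree with each other, the article ranks desire as secondary, and no reader who checks the table would be misled for long. Much of this stands: the document leans clearly to the FSFI, and it would be wrong to give the single sentence equal weight. But the article does not acknowledge the slip, and an unseen analysis plan cannot make both statements true.

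A second reply is that score-level detail is commonly left to the full protocol or analysis plan. That is fair as far as it goes, and a missing score definition alone would not be a finding in a condensed article. The score matters here because the article states a construct that matches only one domain of the instrument it lists as primary. That mismatch is in the text itself.

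Some stronger readings are tempting, and the article does not support them:

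- *Several primary outcomes are planned.* A reader might infer this from the plural heading in Table 1, or from the remark in the Statistical Analysis Plan that response will be judged on multiple measures. The heading has a single row, and the matching section heading is singular. The remark goes on to separate primary from secondary efficacy analyses.
- *Three candidate primaries, hence 1 − 0.95³ = 14.3%.* This counts the FSFI total and its satisfaction domain as independent tests. The domain is a component of the FSFI, so they cannot be. The contradiction is between two instruments.
- *The FSDQ cannot measure satisfaction.* The article gives domain names and no items. It supports only the statement that no listed domain carries that name.
- *The power statement fails because of this contradiction.* The effect size of 0.5 is indeed tied to no instrument, but that is a separate matter, and correcting the Study Measures sentence would not change it.

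**Conclusion.** The point holds as an internal contradiction. Study Measures names the FSDQ for the primary outcome, while Table 1 and the instrument sections name the FSFI and rank the FSDQ as secondary. The FSFI is the better-supported reading. Adopting it still leaves the stated construct, satisfaction, matched to one of six domains, with no statement of which score is primary.

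The size is a potential false-positive rate of about 7.0% to 9.5% against a nominal 5%, for assumed correlations of 0.9 to 0.3, and 9.75% under independence. This rests on three assumptions: two-sided tests, correlations that the article does not supply, and a choice of instrument made after results are seen. The article does not propose such a choice, so the figures illustrate what is at stake and do not estimate an error rate for this trial.

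The article leaves confirmation to a later, larger randomised trial. That lowers the stakes somewhat, but an efficacy study with a declared primary outcome still needs that outcome to be identifiable. The correction should be made before analysis.

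**What to change.** Before data are analysed:

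1. In Study Measures, replace the FSDQ with the FSFI as the instrument for the primary outcome.
2. State one FSFI score as the sole primary outcome, tested at 0.05, by one of two routes:
   - the satisfaction domain, which matches the stated construct and needs no renaming; or
   - the total, with the primary outcome renamed sexual function in the Abstract, the Introduction, Study Measures and the Statistical Analysis Plan.
3. Name the chosen score in the Statistical Analysis Plan section, and state that the FSDQ and all other scores are secondary and cannot replace the primary if it fails.

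The cost is a wording correction. Table 1 schedules both instruments at every assessment in both groups, so no new data, visits or participants are needed.

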**Enrolment**					
Consent and screen	X		X		
Allocation	X		X		
**Structured Interviews**					
MINI for DSM-5	X		X		
DART module	X		X		
**Primary Outcomes**					
Female Sexual Function Index	X	X	X	X	X
**Secondary Outcomes**					
Female Sexual Distress Scale-Revised	X	X	X	X	X
Female Sexual Desire Questionnaire	X	X	X	X	X
Hamilton Anxiety Rating Scale	X	X	X	X	X
Hot Flash Related Daily Interference Scale	X	X	X	X	X
Beck Depression Inventory-II	X	X	X	X	X
Couples Satisfaction Index	X	X	X	X	X
36-Item Short-Form Health Survey	X	X	X	X	X
Dresden Body Image Questionnaire	X	X	X	X	X
Cognitive Flexibility Inventory	X	X	X	X	X
**Other factors**					
Demographics Questionnaire	X		X		

*CBT-SC-PERI, Cognitive Behavioral Therapy for Sexual Concerns During Perimenopause; MINI, Mini International Neuropsychiatric Interview; DART, Diagnostic and Assessment Research Tool*.

### Primary Outcome

#### The Female Sexual Function Index

The Female Sexual Function Index (FSFI) (23) is a six-domain measure of female sexual functioning including sexual desire, subjective arousal, lubrication, orgasm, satisfaction, and pain. The FSFI has demonstrated excellent internal consistency (α = 0.82–0.96) and test-retest reliability when used in menopausal women (22–24). A clinical cut-off score of 26 or lower has been suggested to identify significant sexual dysfunction (22). The FSFI is considered as a gold-standard in assessing sexual functioning in women (25).

### Secondary Outcomes

#### Female Sexual Distress Scale-Revised

The Female Sexual Distress Scale-Revised (FSDS-R) (26) is a 13-item self-report questionnaire assessing various aspects of sexual distress, with a clinical cut-off score of 11 indicated sexual distress. The FSDS-R has demonstrated excellent internal consistency (α = 0.86) and high test-retest reliability (26).

#### Female Sexual Desire Questionnaire

The Female Sexual Desire Questionnaire (FSDQ) (27) is a 50-item self-report questionnaire assessing one's experience of and sexual desire for women across six domains: dyadic desire, solitary desire, resistance, positive relationship, sexual self-image, and concern. The FSDQ has demonstrated excellent internal consistency across domains (α = 0.80–0.92) and specifically measures both dyadic and solitary desire, which other questionnaires do not (27).

#### The Greene Climacteric Scale

The Greene Climacteric Scale (GCS) (28) is a self-report questionnaire measuring four menopause-related domains: vasomotor symptoms, depression and anxiety, physical complaints, and sexual concerns. The GCS has demonstrated good internal consistency (α = 0.73–0.90) during the menopausal transition (29).

#### The Hot Flash Related Daily Interference Scale

The Hot Flash Related Daily Interference Scale (HFRDIS) (30) assesses the degree to which vasomotor symptoms interfere with daily life. The HFRDIS has demonstrated excellent internal consistency (α > 0.92–0.96) in the literature (30, 31).

#### The Beck Depression Inventory-II

The Beck Depression Inventory-II (BDI-II) (32) is a self-report questionnaire and one of the most widely used tools for measuring depression. The BDI-II has demonstrated excellent internal consistency across studies (α = 0.83–0.96) and is among the most widely used self-report measures for depression symptom severity (33).

#### The Hamilton Anxiety Scale

The Hamilton Anxiety Scale (HAM-A) (34) is a clinician administered questionnaire developed to quantify the severity of anxiety symptomatology across 14 items assessing psychic (i.e., mental agitation, distress) and somatic (i.e., physical complaints) anxiety. The HAM-A has demonstrated good validity and reliability in both anxiety and depression populations and is considered a gold-standard (35).

#### The Couples Satisfaction Index

The Couples Satisfaction Index (CSI) (36) is a 32-item scale designed to measure one's satisfaction in a relationship. Items are scored on a seven-point Likert scale in which respondents indicate their degree of “happiness, all things considered, of your relationship,” with responses ranging from 0 (extremely unhappy) to 6 (perfect). The CSI has demonstrated excellent internal consistency [α = 0.96–0.98; (36, 37)]. As this questionnaire assesses relationship satisfaction, participants who are not in a relationship during the study will not complete this questionnaire.

#### 36-Item Short-Form Health Survey

The 36-Item Short-Form Health Survey (SF-36) (38) is a 36-item self-administered questionnaire assessing one's perception of overall health and well-being. The SF-36 has demonstrated excellent internal consistency (α = 0.79–0.94) for both total and subscale scores (39, 40).

#### Dresden Body Image Questionnaire

The Dresden Body Image Questionnaire (DBIQ) (41) is a 35-item self-report questionnaire assessing one's feelings of their physical appearance across five subscales: body acceptance, sexual fulfillment, physical contact, vitality, and self-aggrandizement. The DBIQ has demonstrated excellent internal consistency (α = 0.80–0.94) for total and subscale scores (41, 42) and test-retest reliability (41).

